#### Secondary outcomes

Secondary outcomes will be assessed at 18 weeks, 52 weeks and 104 weeks, or earlier if a preliminary endpoint is reached. Secondary outcomes include:

The number of patients with improvement on disability equal or more than the MCIDTime to MCID improvement on disabilityMean change in disabilityMean change in grip strengthMean change in muscle strengthMean change in sensory impairmentMean change in fatigueMean change in painMean change in health-related quality of life (HRQL)Care use and overall healthcare-related costsNumber of (S) AEs (including corticosteroid associated AEs), as defined in the ‘Adverse event reporting and harms {22}’ section

#### Outcome measures

For disability, we will use the I-RODS and the INCAT-DS. The I-RODS is a patient self-report linearly weighted scale that measures activity and social participation limitations [12, 15]. The I-RODS consists of 24 questions and allows for three response options: (0) impossible to perform, (1) performed with difficulty and (2) easily performed. Scores range from ‘0’ (all activities impossible to perform) to ‘48’ (all activities easily performed). These scores are transformed and expressed in log-odds (logits), ranging from − 6.95 to 8.11. The I-RODS has been developed specifically for inflammatory neuropathies including CIDP and has been validated in a large group of patients [16]. In addition, disability will be measured using the adjusted INCAT-DS, which has been used in numerous CIDP trials [5, 13, 17]. The adjusted INCAT-DS is a 10-point ordinal scale measuring limb disability, ranging from ‘0’ (no arm or leg disability) to ‘10’ (no arm movement possible, wheelchair bound). The reason to choose both disability scales to assess improvement and remission is outlined in the discussion. We will use a handheld Vigorimeter to measure grip strength in kPa, the Medical Research Council (MRC) sum score of 12 predefined muscle groups (including shoulder abduction, elbow flexion, wrist extension, hip flexion, knee extension and foot dorsiflexion) to measure muscle strength, the INCAT- sensory sum score (INCAT-SS) to assess sensory impairment, the Rasch-built Fatigue Severity Scale (R-FSS), the Pain intensity numeric rating scale (PI-NRS) and the EuroQol (EQ-5D-5L) to measure HRQL [18–24]. Health care resources will be measured using working documents and the iMTA Medical Consumption Questionnaire (*i*MCQ) and the Productivity Cost Questionnaire (*i*PCQ), both adapted to the study population [25, 26]. Working documents keep track of IVIg use, outpatient hospital consultations, hospitalizations, and major diagnostic examinations and therapeutic interventions. Tailored *i*MCQ will be used to measure volume of out-of-hospital consultations (general physician, physical therapist, psychologist, etc.), other institutionalizations (temporary rehabilitation, nursing home), day-care treatment, emergency admissions and out-of-pocket expenses by patients. The impact of CIDP on the ability of a person to perform work, production loss following absence from work or personal inefficiencies will be measured with the *i*PCQ. AEs reported spontaneously at visits or otherwise reported by patient or observed by physician, during the first 24 weeks of the study, or in the case of an early endpoint during treatment protocol within 6 weeks of last treatment course, are recorded using an AE template provided by the Amsterdam UMC, Clinical Research Unit (CRU). The AE template consist of a description, severity score (mild, moderate, severe), potential relation to IMP (unlikely, unlikely, possible, probable, definite, not possible to assess), consequences for IMP administration (options including temporary or permanent stops, dose changes), any other actions taken (i.e. start of co-medication, a referral) and the outcome (i.e. resolved). Severity scores will be defined as followed: mild (i.e. an AE that is transient and may require only minimal treatment or therapeutic intervention; the event does not generally interfere with usual activities of daily living), moderate (i.e. alleviated with specific therapeutic intervention; the event interferes with usual activities of daily living, causing discomfort but poses no significant or permanent risk of harm to the research patient) or severe (i.e. an AE that interrupts usual activities of daily living, or significantly affects clinical status, or may require intensive therapeutic intervention). Patients will complete a structured questionnaire with most frequent corticosteroid and IVIg-related AEs at the 18-week visit. These AEs are subsequently scored by the investigator using the previously described severity score. (S)AEs are further described under the ‘Adverse event reporting and harms {22}’ section. Long-term corticosteroid related AEs are also assessed by the investigator at weeks 52 and 104. AE questionnaires are completed after all other outcome assessments have been performed. Patients are asked to indicate which treatment they think they have received, at the end of the study. Outcome measures and assessment visits are listed under the ‘Plans for assessment and collection of outcomes {18a}’ section and shown in Table 1.

**Table 1 Tab1:** Study visits and measurements

	Study visits							
	Intervention period (in weeks)				Follow-up period (in weeks)		Safety follow-up (in weeks)	Unscheduled visits (in weeks)
Measurements	BL	6	12	18	24	52	104	0–52
**Blood pressure**	X	X	X	X	X	X		X*
**Body weight**	X			X		X		X*
**HbA1C**	X				X	X		
**AEs**	X	X	X	X	X			X^‡^
**AE questionnaire**^**§**^				X		X	X	X^*¥^
**I-RODS**	X	X	X	X	X	X	X	X
**INCAT-DS**	X	X	X	X	X	X	X	X
**Grip strength**	X	X	X	X	X	X		X
**MRC sum score**	X	X	X	X	X	X		X
**INCAT-SS**	X	X		X		X		X*
**EuroQol**	X	X		X		X		X*
***i*****MCQ**		X		X		X		X*
***i*****PCQ**		X		X		X		X*
**R-FSS**	X	X		X		X		X*
**PI-NRS**	X	X		X		X		X*

*Abbreviations: BL* baseline, *AE* adverse event, *I-RODS* inflammatory Rasch Disability Scale, *MRC* Medical Research Council, *INCAT-DS* Inflammatory Neuropathy Cause and Treatment Disability Scale, *INCAT-SS* Inflammatory Neuropathy Cause and Treatment sensory sum score, *iMCQ* iMTA Medical Consumption Questionnaire, *iPCQ* iMTA Productivity Cost Questionnaire, *R-FSS* Rasch-built Fatigue Severity Scale, *PI-NRS* pain intensity numeric rating scale. *If the unscheduled visit is considered as a preliminary endpoint visit. ^**§**^This row includes the investigator assessed (long-term) AEs investigated at weeks 52 and 104. ^‡^If unscheduled visits takes place during treatment protocol, within 6 weeks of ending treatment protocol. ^¥^In case of a preliminary endpoint during intervention period, week 18 AE questionnaire is completed by patient and physician

### Participant timeline {13}

Total follow-up is 104 weeks (2 years). After the intervention period of 18 weeks, patients will be followed for another 86 weeks during which treatment will be given only in case of deterioration by at least the MCID on the I-RODS and/or deterioration (i.e. increase) of at least one point on the adjusted INCAT-DS. Choice of treatment in case of relapse is at discretion of the treating physician. If a change of treatment regimen is regarded necessary during the 18 weeks’ intervention period, trial medication will be stopped but further follow-up will continue as scheduled. Additional (ad hoc) visits, i.e. if a relapse is suspected, can be scheduled at discretion of treating physician. Treatment protocol and follow-up are illustrated in Fig. 1.

### Sample size {14}

There are no robust figures on the long-term remission rates in patients treated with IVIg only. In a previous trial, remission during a 6-month period was seen in about half of IVIg responders, compared to 100% in IVMP responders [9]. However, a significant proportion of patients were not treatment naïve but known responders to IVIg. Furthermore, follow-up was shorter than the follow-up period in this study. We assume that the remission rate after IVIg is approximately 35% during an 8-month follow-up period. Treatment-naïve CIDP patients treated with dexamethasone had a long-term remission rate of 56% using a more stringent definition of improvement compared to this study [5, 8]. Our limited prospective pilot data of the OPTIC protocol suggest similar remission rates (59%) [10]. We assume remission rates of 35% in the IVIg/placebo group, and 65% in the IVIg/IVMP. A 30% difference in remission rate is large but warranted as IVMP may lead to various AEs in patients and because there is the alternative of continuing maintenance IVIg treatment. A two-group chi-square test with a 0.05 two-sided significance level will have 80% power to detect the difference between a control group proportion (IVIg/placebo) of 0.35 and a treatment group proportion (IVIg/IVMP) of 0.65 (odds ratio of 3.45) when the sample size in each group is 43 (86 patients in total). Anticipating on a 10% attrition rate due to AEs, we will include 48 (43/0.90) patients in each group (96 patients in total).

### Recruitment {15}

Participants are enrolled in both tertiary referral centres as well as large general neurology clinics, with an adequate geographical spread in both the Netherlands and the UK. Design of the trial, with IVMP as an addition to standard care IVIg, and limited clinic visits over the 104-week course of the trial promote trial enrolment. Frequent trial updates in the form of newsletters and presentations at (inter) national (neuromuscular) conferences as well as patient events promote trial visibility amongst referring neurologists and participants.

### Assignment of interventions: allocation

#### Sequence generation {16a}

After signing the IC form, patients are randomised to either IVIg + IVMP or IVIg + placebo. Randomisation is performed using the functionality of Castor EDC. Randomisation is stratified per country (NL/UK) and previously administered treatment (treatment naïve versus previously treatment, inclusion group 2) with random permuted blocks of sizes 2 or 4 within the strata.

#### Concealment mechanism {16b}

Investigators and other study staff are unable to view treatment allocation in Castor EDC. Only the pharmacists are able to view treatment allocation in Castor EDC. A specifically designated co-investigator is the only person able to change user rights in the Castor EDC database. The database software (audit trail) automatically logs these changes. Randomisation code is provided to the pharmacist of the participating centre automatically through Castor following randomisation.

#### Implementation {16c}

Treating neurologists or assigned (GCP trained) delegates are allowed to enrol participants. To randomise a patient, local investigator provides patient’s personal identification number (PIN) and treatment status (previously treated versus treatment naïve) to the coordinating investigator (or assigned delegate) who will perform randomisation.

### Assignment of interventions: blinding

#### Who will be blinded {17a}

Patients, relatives, IMP administering nurses (in hospitals, day care centres, home-care), treating and evaluating physicians will be blinded for treatment allocation. The blind will be maintained until the whole study is completed.

#### Procedure for unblinding if needed {17b}

Pharmacists will be the only persons able to break the randomisation code. The randomisation code will be broken after the last follow-up visit of the last patient, after data cleaning and database lock. The randomisation code can be broken during the first 18 weeks if unblinding is judged necessary by treating physician to start additional treatment or to change the treatment regimen. These patients will be considered treatment failures and will reach a preliminary endpoint. All secondary outcome measurements will be performed before the blind is broken. In these cases, the coordinating PI will remain blinded. Treatment allocation will not be revealed in patients who are considered a treatment failure, but do not need or do not wish to receive additional treatment.

The randomisation code can be broken if a relation between trial treatment and a SAE is suspected and if knowledge of treatment allocation is deemed necessary by local investigator or treating physician. In case of a Suspected Unexpected Serious Adverse Reaction (SUSAR), the investigator will send an Unblinding Request Form (URF) to the coordinating PI and make every effort to contact the coordinating PI to discuss options. If unblinding is deemed necessary, coordinating PI will send the URF to the study pharmacist. The study pharmacist will reveal treatment allocation of the individual patient to an independent physician on the unblinding form (UF) to ensure continued blinding of local investigator and treating physician. The UF must include the date, time and reason for unblinding. This information will be recorded in the eCRF and local source documents. If the blind is broken, the patient must be discontinued from study medication as soon as possible. The patient will be encouraged to perform an end of study assessment and be under medical supervision until symptoms cease or the condition becomes stable. An independent physician will document the SUSAR in the appropriate Dutch module (ToetsingsOnline) in order to maintain the blind for other research team members.

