### Provisions for post-trial care {30}

After study completion, patients will continue to receive standard care for CIDP. Patient who are stable will not require additional treatment. Patients who reach a preliminary endpoint, defined as deterioration during the 18-week treatment period requiring additional CIDP treatment, no improvement at week 18, restart CIDP treatment for any reason (i.e. a relapse) between week 18–52 or drop out during study for whatever reason will be treated at physician’s discretion and will complete follow-up visits according to protocol. AMC Medical Research BV (AMR) has an insurance which is in accordance with the legal requirements in the Netherlands (Article 7 of the Medical Research Involving Human Subjects Act (WMO) and the Measure regarding Compulsory Insurance for Clinical Research in Humans of 23 June 2003). This insurance provides cover for damage to research patients through injury or death caused by the study for patients in the Netherlands. Where harm to participants arises from the conduct of the research, National Health Services (NHS) indemnity applies. Where harm to participants comes from the design or management of the research, this comes under Sponsor insurance. These arrangements are covered in a coordinator agreement and in the site agreements.

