### Outcomes {12}

#### Primary outcome

The primary outcome is the number of patients in remission at 52 weeks after start of treatment. Remission is defined as sustained improvement without the need for further treatment. Improvement is defined as improvement by at least the minimal clinical important difference (MCID) on the inflammatory Rasch-Overall Disability Scale (I-RODS) and/or improvement of one or more points on the adjusted Inflammatory Neuropathy Cause and Treatment Disability Scale (INCAT-DS) at 18 weeks (end of treatment) compared to baseline. For the I-RODS, MCID is calculated using a statistical approach in which an increase of 1.96 SE is considered relevant improvement [12]. For the adjusted INCAT-DS, a decrease of 1 point or more is considered a relevant improvement [13, 14]. Changes in upper limb function from ‘0’ (normal) to ‘1’ (minor symptoms) or from ‘1’ to ‘0’ are not considered relevant deterioration or improvement [13]. Sustained is defined as no deterioration between 18 and 52 weeks, i.e. difference on the I-RODS of less than the MCID difference and/or less than one point on the adjusted INCAT-DS. Patients will be considered a treatment failure if they (1) received additional CIDP treatment during the 18-week intervention period, (2) do not improve at 18 weeks, (3) restart CIDP treatment for any reason between 18 and 52 weeks, or (4) do not show a sustained improvement at 52 weeks as defined above.

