#### Methods in analysis to handle protocol non-adherence and any statistical methods to handle missing data {20c}

In the ITT analysis, all randomised patients will be analysed in the treatment group to which they were originally allocated, irrespective of potential eligibility deviation, unblinding, non-adherence or other deviations from protocol. In the PP analysis, patients will be analysed who were included in accordance with the study protocol and who completed the treatment originally allocated. Patients in whom protocol deviations occurred will be excluded from the per protocol population, with the exception of the following deviations: patients having missed one IMP and/or IVIg administration, patients who receive their treatment out of window (up to 7 days) or patients with deviations on an infusion-administration level (i.e. partial IMP or IVIg administration (single infusion), IMP administration infused faster than the required 1 h).

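### The unblinding section fails patients unblinded for a change of regimen, a criterion that the primary outcome's failure list does not contain

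*Protocol article*

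**What the plan says.** The Primary outcome section gives a numbered list of failure criteria. The first is: "Patients will be considered a treatment failure if they (1) received additional CIDP treatment during the 18-week intervention period". The second and third are that patients "do not improve at 18 weeks, (3) restart CIDP treatment for any reason between 18 and 52 weeks". The fourth is that they "do not show a sustained improvement at 52 weeks as defined above". Section {30}, Provisions for post-trial care, separately defines the preliminary endpoint. For the treatment period it names "deterioration during the 18-week treatment period requiring additional CIDP treatment", and it goes on to no improvement at week 18, restart of treatment in weeks 18 to 52, and drop-out. Neither list mentions unblinding or a change of regimen.

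Section {17b} allows the code to be broken in the first 18 weeks "if unblinding is judged necessary by treating physician to start additional treatment or to change the treatment regimen". It then sets an outcome for those patients: "These patients will be considered treatment failures and will reach a preliminary endpoint".

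Elsewhere a regimen change carries no failure rule:

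- Section {11b} (study drug) and section {11d} (IVIg) allow changes for adverse events or contra-indications and log them as protocol deviations.
- Section {13} says that trial medication stops on a change of regimen and follow-up continues.
- The second paragraph of {17b}, on code breaks for a suspected treatment-related serious adverse event, stops study medication but does not say how the primary outcome is scored.

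**The concern.** The primary outcome is a count of patients in remission, so the rule that turns a patient into a failure has to stand in one place and give one answer. Here two sections each state a rule, and one is wider than the other. For a patient who falls between them, the outcome would depend on whether the treating physician broke the code, and not on the course of the disease. Two statisticians who each followed the protocol could report different counts. The trial plans 48 patients per arm, so a handful of such patients would be visible in the result.

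**Working it through.** **Comparing the rules by reason for the code break (weeks 0 to 18)**

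| Reason | Primary outcome section | Section {17b} | Agree? |
|---|---|---|---|
| To start additional CIDP treatment | Failure, criterion 1 | Failure | Yes |
| To change the regimen, no additional CIDP treatment | Scored on criteria 2 to 4 | Failure | Not if the patient otherwise remits |
| Suspected treatment-related SAE | Scored on criteria 1 to 4 | No failure rule stated | No conflict stated |

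**Test case.** Take a patient whose regimen is changed for an adverse event, who receives no additional CIDP treatment, is improved at week 18, and is stable and untreated to week 52. None of the four criteria is met, so the Primary outcome section gives remission. If the code was broken to make that change, {17b} gives failure. If the code was not broken, {17b} is silent and remission stands. A patient who fails on criteria 2 to 4 anyway is scored the same under both sections.

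**The plan's own figure.** Inputs from Sample size {14}: 35% against 65%, two-sided 0.05, 43 per group, raised to 48.

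Power = Φ[(d − 1.96·SE0)/SE1], where SE0 = √(2·p̄(1−p̄)/n) and SE1 = √((p1(1−p1) + p2(1−p2))/n).

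- n = 43: SE0 = √(0.50/43) = 0.1078 and SE1 = √(0.455/43) = 0.1029. (0.30 − 0.2113)/0.1029 = 0.862, so power is 80.6%. The stated 80% reproduces.
- 43/0.90 = 47.8, so 48 per group. The same formula at 48 gives 84.8%.

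**Illustrative size.** The document gives no rate for code breaks of this kind. Let q be the assumed share of an arm recoded to failure whatever their course, so that the remission rate becomes p(1 − q). The top value, 10%, borrows the attrition rate in {14}. Power at 48 per arm:

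| q | Both arms | IVMP arm only | Placebo arm only |
|---|---|---|---|
| 0 | 84.8% | 84.8% | 84.8% |
| 2% | 83.2% | 81.3% | 86.5% |
| 5% | 80.8% | 75.4% | 88.8% |
| 10% | 76.6% | 64.0% | 92.0% |

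For example, with 5% in the IVMP arm only, 0.65 × 0.95 = 0.6175, and 0.6175 against 0.35 gives 75.4%.

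In single patients, one recoded remitter moves an arm by 1/48 = 2.1 points. If that patient is in the IVMP arm, 0.65 − 1/48 = 0.629 against 0.35 gives 79.0%. At about the expected result, 31/48 against 17/48, the uncorrected chi-square p is 0.004. Recoding four IVMP remitters (27/48) gives 0.041, and recoding five (26/48) gives 0.065.

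**The case against.** The best reply is that the gap hardly opens in practice. The first paragraph of {17b} ends by saying that allocation is not revealed to treatment failures who neither need nor want additional treatment, which ties these code breaks to additional treatment and so to criterion 1. The emergency unblinding text says that knowing the allocation would not change the management of corticosteroid complications, and it names clinical deterioration as the situation that might require unblinding. Section {22} gives a switch to plasmapheresis as its example of stopping early. On that reading, a change of regimen means a switch of CIDP treatment after deterioration, and all sections agree. It can also be said that counting unblinded patients as failures is a recognised choice when the outcome rests partly on self-report, as the I-RODS does.

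Much of this stands, and it makes such cases probably few. It does not close the gap. Section {17b} joins the two branches with an or, so the second branch should add something to the first, and {11b} and {11d} use regimen change for adverse events and contra-indications. If the narrow meaning is intended, no sentence says so. If failing unblinded patients is a deliberate choice, it belongs in the outcome definition.

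Two stronger readings are tempting and are not supported. A reader might infer that the rule biases the comparison against IVMP, because drug effects are likelier there. The document gives no distribution of these code breaks by arm. The protocol abstract's Discussion expects some IVIg non-responders to respond to corticosteroids, so deterioration could equally put them in the placebo arm, where recoding raises power. A reader might also see a conflict with {20c}, which analyses patients "irrespective of potential eligibility deviation, unblinding, non-adherence or other deviations from protocol". That text fixes the arm in which a patient is analysed, not the outcome the patient is given.

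**Conclusion.** The point holds as an inconsistency between two stated rules for the primary outcome. It is confined to code breaks in weeks 0 to 18 made to change the regimen without additional CIDP treatment, in patients who would otherwise meet the remission definition. Each such patient is worth 2.1 points in one arm. The power figures rest on the planned 35% and 65%, on 48 analysed per arm, and on assumed shares and arms, and they show only that the result would be sensitive to a few patients. They do not predict a loss of power or a direction of bias. The inconsistency is worth removing before database lock because it concerns who counts as an event and costs almost nothing to settle.

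**What to change.** Reconcile the Primary outcome section with {30}, {13} and {17b} into one failure list, placed in the primary outcome and applied whether or not the code was broken. The list should state whether a regimen change without additional CIDP treatment counts, and should define regimen change so that it reads the same way in {11b}, {11d} and {13}. Section {17b}, for both the first-paragraph and the SAE routes, should refer to that list and set no scoring rule of its own. Which criterion to adopt is for the investigators.

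List the unblinded patients with the reason for each code break, and add a sensitivity analysis of the primary outcome in which they are scored the other way.

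The cost is a few sentences in the protocol and one extra analysis. If regimen change is not made a criterion, the small downside is that a few unblinded patients are scored partly on self-report; the sensitivity analysis shows how much that matters.
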